## 5 STUDY POPULATION

### 5.1 INCLUSION CRITERIA

To be eligible to participate in this study, an individual must meet all of the following criteria at screening (any assessments included in the Schedule of Events [Section 1.3] on Cycle 1 Day 1 must also continue to be met for the patient to remain eligible):

1. Provision to sign and date the consent form.
2. Able to comply with all study procedures and be available for the duration of the study in the Investigator's judgment.
3. Age  $\geq 18$  years on the day of signing informed consent
4. If in Cohort A, the patient must state willingness to undergo pre- and post-treatment biopsies. According to the Investigator's judgement, the planned biopsies should not expose the patient to substantially increased risk of complications.
5. Eastern Cooperative Oncology Group (ECOG) performance status of 0 or 1.
6. Histologically confirmed unresectable metastatic colorectal adenocarcinoma.
  - All primary tumor locations are allowed
  - Measurement of EGFR expression by immunohistochemistry is not required
7. Progression on at least two prior lines of therapy for unresectable metastatic colorectal adenocarcinoma.
  - A patient who progressed on a single line of therapy including a fluoropyrimidine, oxaliplatin, and irinotecan for unresectable metastatic colorectal adenocarcinoma (e.g., FOLFIRINOX or FOLFOXIRI) is eligible.
  - Previous administration of anti-EGFR drugs does not impact eligibility, except as listed in Exclusion Criterion #15.
8. Microsatellite stable or proficient mismatch repair status documented (only one of these criteria is needed, however if one criterion is met and one is not met then the patient is excluded)
9. Measurable disease, according to RECIST v1.1. Previously irradiated lesions are not considered measurable unless progression has been documented in the lesion. Note that lesions intended to be biopsied should not be target lesions.
10. Adequate hematologic and end organ function, defined by the following laboratory results:
  - $ANC \geq 1.5 \times 10^9/L$
  - Platelet count  $\geq 100 \times 10^9/L$
  - Hemoglobin  $\geq 9$  g/dL without transfusion in the previous week
  - Serum bilirubin  $\leq 1.5 \times$  the upper limit of normal (ULN); patients with known Gilbert's disease may have a bilirubin  $\leq 3.0 \times ULN$

- AST, ALT, and alkaline phosphatase (ALP)  $\leq 3 \times \text{ULN}$  with the following exceptions:

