    - Patients with documented liver metastases: AST and/or ALT  $\leq 5 \times \text{ULN}$
    - Patients with documented liver or bone metastases: ALP  $\leq 5 \times \text{ULN}$
  - Creatinine clearance  $\geq 50 \text{ mL/min}$  as calculated using the Cockcroft-Gault formula or measured using a 24-hour urine collection
  - International normalized ratio (INR) OR prothrombin time (PT)  $\leq 1.5 \times \text{ULN}$  unless participant is receiving anticoagulant therapy as long as INR or PT is within expected or therapeutic range of intended use of anticoagulants
  - Activated partial thromboplastin time (aPTT)  $\leq 1.5 \times \text{ULN}$  unless participant is receiving anticoagulant therapy as long as aPTT is within expected or therapeutic range of intended use of anticoagulants
11. QTcF interval of  $\leq 480 \text{ msec}$  (Based upon value from the screening ECG).
12. Serum pregnancy test (for females of childbearing potential) negative at screening and at C1D1. A woman is considered fertile (woman of childbearing potential, “WOCBP”) following menarche and until becoming post-menopausal unless permanently sterile. Women in the following categories are not considered WOCBP:
- Premenarchal
  - Premenopausal female with one of the following: documented hysterectomy, documented bilateral salpingectomy, documented bilateral oophorectomy (note: documentation can come from the site personnel’s review of the participant’s medical records, medical examination, or medical history interview)
  - Postmenopausal female. A postmenopausal state is defined as no menses for 12 months without an alternative medical cause. A high follicle stimulating hormone (FSH) level in the postmenopausal range may be used to confirm a postmenopausal state in women not using hormonal contraception or hormonal replacement therapy (HRT). However, in the absence of 12 months of amenorrhea, confirmation with two FSH measurements in the postmenopausal range is required. Females on HRT and whose menopausal status is in doubt will be required to use one of the non-hormonal highly effective contraception methods if they wish to continue their HRT during the study. Otherwise, they must discontinue HRT to allow confirmation of postmenopausal status before study enrollment.

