### 12.1.6 MANAGEMENT OF HEPATOTOXICITY

Hepatotoxicity may be due to evorpacept (ALX148), cetuximab, or pembrolizumab, and may be immune-mediated.

| Event                                                                                                                | Guidance                                                                                                                                                             |
|----------------------------------------------------------------------------------------------------------------------|----------------------------------------------------------------------------------------------------------------------------------------------------------------------|
| Grade 1:
AST or ALT >ULN - 3.0 x ULN if baseline was normal; 1.5 - 3.0 x baseline if baseline was abnormal and/or | 
 
• Continue evorpacept (ALX148), cetuximab, and pembrolizumab
 
• Continue with the standard monitoring plan
 
 |

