| 
Total bilirubin >ULN - 1.5 x ULN if baseline was normal; > 1.0 - 1.5 x baseline if baseline was abnormal
                                                                                                                                         |                                                                                                                                                                                                                                                                                                                                                                                                                                                                                                                                                                                                                                                                                                                                                                                                                                                                                                                                                                                                                                                                                                                                                                                                                                                                                                                                                |

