| 
Grade 2:
AST or ALT >3.0 - 5.0 x ULN if baseline was normal; >3.0 - 5.0 x baseline if baseline was abnormal
and/or
Total bilirubin >1.5 - 3.0 x ULN if baseline was normal; >1.5 - 3.0 x baseline if baseline was abnormal
     | 
 
• Permanently discontinue study treatments if AST or ALT > 3x upper limit of normal (ULN) AND total bilirubin >2 x ULN, unless clear evidence of biliary obstruction exists
 
• Otherwise, continue evorpacept (ALX148) and cetuximab (may hold at Investigator discretion) and HOLD pembrolizumab 
 
• Consider administering 0.5-1 mg/kg/day oral prednisone or equivalent followed by ≥ 1-month taper
 
• If event resolves to Grade 1 or better within 2 weeks, may consider resuming pembrolizumab at fixed dose at discretion of investigator and medical monitor.a,b,c
 
 
 
• Permanently discontinue pembrolizumab if event does not resolve to Grade 1 or baseline or better within 2 weeks (unless otherwise agreed between the Investigator and AGICC)a,b,c
 
• Monitor LFTs at least weekly.
 
                                                                                                                                                                                                                                                                                                                                                                                |

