| 
Grade 3:
AST or ALT >5.0 - 20.0 x ULN if baseline was normal; >5.0 - 20.0 x baseline if baseline was abnormal
and/or
Total bilirubin >3.0 - 10.0 x ULN if baseline was normal; >3.0 - 10.0 x baseline if baseline was abnormal
 | 
 
• Permanently discontinue study treatments if AST or ALT > 3x upper limit of normal (ULN) AND total bilirubin >2 x ULN, unless clear evidence of biliary obstruction exists
 
• Otherwise, hold evorpacept (ALX148), cetuximab, and pembrolizumab
 
• Refer to a hepatologist and consider liver biopsy.
 
• Consider administering 1-2 mg/kg/day oral prednisone or equivalent followed by ≥ 1 month taper (for possible autoimmune hepatitis).
 
• If LFTs do not decrease within 48 hr after initiation of systemic steroids, consider adding an immunosuppressive agent (e.g., mycophenolate or TNF-antagonist). Infliximab might not be the most appropriate treatment option for immune mediated hepatitis given the risk for liver failure
 
• Monitor LFTs every 48-72 hours until decreasing and then follow weekly.
 
• Permanently discontinue study treatments for life-threatening hepatic events and contact the Medical Monitor.
 
• Permanently discontinue pembrolizumab. Restart evorpacept (ALX148, at one dose level reduction) and cetuximab (dose determined by institutional guidelines) once resolved to grade 1 or baseline or better, per Investigator discretion after discussion with the medical monitor
 
 |

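### In 12.1.6 the permanent stop for AST/ALT >3 x ULN with bilirubin >2 x ULN is missing from the Grade 1 row, which eligible patients with raised baselines can occupy while meeting it

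*Protocol*

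**What the plan says.** The hepatotoxicity table in Protocol 12.1.6 assigns an action to each grade.

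- **Grade 1.** With an abnormal baseline, the AST/ALT band is "1.5 - 3.0 x baseline if baseline was abnormal" and the bilirubin band is above "1.0 - 1.5 x baseline if baseline was abnormal". The action is "Continue evorpacept (ALX148), cetuximab, and pembrolizumab", with standard monitoring.
- **Grades 2 and 3.** Both rows open with "Permanently discontinue study treatments if AST or ALT" exceeds 3 x ULN and total bilirubin exceeds 2 x ULN, unless biliary obstruction is clear. Only if that is not met do the milder instructions apply; in the Grade 3 row this is "Otherwise, hold evorpacept (ALX148), cetuximab, and pembrolizumab".
- **Grade 4.** Study treatment stops permanently without condition.

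Inclusion criterion 10 (5.1) limits bilirubin to 1.5 x ULN, but "patients with known Gilbert's disease may have a bilirubin" of up to 3.0 x ULN. AST and ALT may be up to 3 x ULN. For "Patients with documented liver metastases: AST and/or ALT" the limit is 5 x ULN.

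**The concern.** The stop is written on one scale (multiples of ULN) and placed in rows reached on another (multiples of the patient's own baseline). If a patient meets the stop but both values are still graded 1, the site reading the table is told to carry on with all three drugs, although the same table requires permanent discontinuation for that combination one row lower.

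This is not explained by a deliberate allowance for abnormal baselines. The Grade 2 row applies the absolute stop to abnormal-baseline patients too, as soon as their grade gets there. At stake is whether a patient stays on three drugs that 12.1.6 itself names as possible causes of liver injury.

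**Working it through.** There is no planned figure to reproduce; this is a consistency check of the table against the entry limits.

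**Inputs.** From 12.1.6: the stop is AST or ALT >3 x ULN and bilirubin >2 x ULN; the Grade 1 ceilings with an abnormal baseline are 3.0 x baseline (AST/ALT) and 1.5 x baseline (bilirubin). From 5.1: the entry limits given above.

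**Step 1: baselines that open the gap.** Both values must be Grade 1 or lower while the stop is met.

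- AST/ALT: 3.0 x baseline > 3 x ULN requires baseline > 3/3.0 = 1.0 x ULN.
- Bilirubin: 1.5 x baseline > 2 x ULN requires baseline > 2/1.5 = 1.33 x ULN.

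If either baseline is normal there is no gap: AST/ALT >3 x ULN or bilirubin >2 x ULN from a normal baseline is already Grade 2, where the stop is printed.

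**Step 2: width of the bilirubin window** (above 2.0 x ULN, up to 1.5 x baseline).

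| Baseline bilirubin (x ULN) | Grade 1 ceiling (x ULN) | Window (x ULN) |
|---|---|---|
| 1.33 | 2.0 | none |
| 1.4 | 1.5 x 1.4 = 2.10 | >2.0 to 2.10 |
| 1.5 (entry limit without Gilbert's) | 1.5 x 1.5 = 2.25 | >2.0 to 2.25 |
| 2.0 (Gilbert's) | 1.5 x 2.0 = 3.0 | >2.0 to 3.0 |

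For AST/ALT the room is wide: up to 3.0 x 3 = 9 x ULN from the ordinary entry limit and 3.0 x 5 = 15 x ULN from the liver-metastasis limit. Bilirubin is therefore what limits the gap.

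**Step 3: an eligible patient in whom both values rise** (no liver metastases, no Gilbert's disease).

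- AST 2.5 to 4.5 x ULN: 4.5/2.5 = 1.8 x baseline, Grade 1.
- Bilirubin 1.5 to 2.2 x ULN: 2.2/1.5 = 1.47 x baseline, Grade 1.
- Stop: 4.5 > 3 and 2.2 > 2, so it is met. The Grade 1 row says continue.

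**Step 4: same current values, two abnormal bilirubin baselines.** AST is 4 x ULN and unchanged (eligible with liver metastases); bilirubin is now 2.05 x ULN.

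- Baseline 1.3: 2.05/1.3 = 1.58 x baseline, Grade 2, permanent stop.
- Baseline 1.4: 2.05/1.4 = 1.46 x baseline, Grade 1, continue.

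The patient with the worse baseline gets the more lenient instruction.

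**Step 5: does other text supply the stop?**

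- 12.1.1 interrupts all drugs at Grade 3 or higher, and for Grades 1 and 2 refers back to the specific tables. Its restart and new-cycle condition is satisfied at baseline or Grade 1.
- 8.5 makes a similar combination an event of clinical interest, to be reported, and notes that such values may need further evaluation. It applies only if ALP is below 2 x ULN, whereas for "Patients with documented liver or bone metastases: ALP" up to 5 x ULN is allowed at entry.
- 4.1.5 lists the same combined values as a DLT, with no grade or baseline qualifier, if related to study drug. It gives no treatment instruction for the patient.
- 7.2 requires discontinuation for a condition that may endanger the patient, and 12.1.1 reserves medical judgment. Neither names these values.

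**The case against.** The strongest reply has three parts.

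First, baseline-relative grading exists so that patients with abnormal baselines are not judged on absolute values. A bilirubin of 2.1 x ULN reached from 1.0 is a 110% rise; from 1.5 it is 40%. A reader might infer that any difference in instruction at identical current values is a defect. The protocol does not support that: different handling of different changes is what relative grading is for. What stands is narrower. Having chosen an absolute stop and applied it to abnormal baselines at Grade 2, the table leaves a strip uncovered, and in Step 4 the two rises (58% and 46%) are not far apart.

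Second, the strip is small. Without Gilbert's disease it needs a bilirubin baseline above 1.33 and at most 1.5 x ULN, an abnormal AST/ALT baseline, and on-study bilirubin no higher than 2.25 x ULN; anything higher is Grade 2. This is correct and limits the importance of the point. In Step 4 AST is also stable, so that case shows the inconsistency rather than a combined rise; Step 3 shows the combined rise.

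Third, the investigator has other safeguards: the DLT definition, the event-of-clinical-interest work-up, the duty to stop when safety is at risk, and medical judgment. These make it less likely that a site would follow the Grade 1 cell blindly. None replaces an explicit stop, and the cell still points the wrong way.

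**Conclusion.** The point holds as a small but real error in a safety rule. The combined stop is absent from a row that eligible patients can occupy while meeting it, and that row says continue. The gap requires both baselines to be abnormal, AST/ALT above ULN and bilirubin above 1.33 x ULN. Without Gilbert's disease it covers bilirubin above 2.0 and at most 2.25 x ULN; with Gilbert's disease it is wider.

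The conclusion assumes that the site grades strictly by the printed bands and that no biliary obstruction is evident. The protocol gives no frequency for such baselines, so no event rate is claimed; few patients are expected.

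Two stronger inferences are not supported. One is that the protocol as a whole directs continued treatment in liver injury: only this cell does, and 7.2 and 12.1.1 still let or require the investigator to stop. The other is that 12.1.6 contradicts 4.1.5: the DLT list serves the dose decision, and its AST/ALT-only limits are on a different scale for that purpose. No endpoint, sample size or analysis is affected.

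**What to change.** Add one line above the 12.1.6 table:

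*At any grade, in patients whose baseline total bilirubin was ≤1.5 x ULN, all study treatments are stopped permanently if AST or ALT is >3 x ULN and total bilirubin is >2 x ULN, with the same exception for biliary obstruction as in the rows below.*

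Leave the Grade 2 and 3 rows as printed, so no stop now required is lost. No change is needed to 4.1.5 or to inclusion criterion 10, and the baseline tests are already collected.

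The cut at 1.5 x ULN means the line always needs a bilirubin rise of more than 33% (2.0/1.5 = 1.33). A cut at 2 x ULN would permanently stop a patient with Gilbert's disease for a move from 1.95 to 2.05 x ULN, about 5%. Patients with Gilbert's disease who enter above 1.5 x ULN stay on the existing rows. The gap remains open for them, but one who enters with, say, AST at 4 and bilirubin at 2.5 x ULN already exceeds both limits and should not be stopped by the new line for an unchanged baseline.

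The cost is a few more permanent discontinuations, including some in patients whose AST/ALT is raised but stable from liver metastases and in whom only bilirubin has moved.

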### 12.1.7 MANAGEMENT OF PNEUMONITIS

Events of pneumonitis have been reported with pembrolizumab and cetuximab. All pulmonary events should be thoroughly evaluated for other commonly reported etiologies such as pneumonia/infection, lymphangitic carcinomatosis, pulmonary embolism, heart failure, chronic obstructive pulmonary disease, or pulmonary hypertension. Pneumonitis has not been reported with evorpaccept (ALX148).

| Event                                                                                        | Guidance                                                                                                                                                                                                                                                                                                                                                                                                                                                                                                                                                                                                                                                                                                                                                                                                                                                                                                                                                                                                     |
|----------------------------------------------------------------------------------------------|--------------------------------------------------------------------------------------------------------------------------------------------------------------------------------------------------------------------------------------------------------------------------------------------------------------------------------------------------------------------------------------------------------------------------------------------------------------------------------------------------------------------------------------------------------------------------------------------------------------------------------------------------------------------------------------------------------------------------------------------------------------------------------------------------------------------------------------------------------------------------------------------------------------------------------------------------------------------------------------------------------------|
| Grade 1 (Asymptomatic; clinical or diagnostic observations only; intervention not indicated) | 
 
• Continue evorpaccept (ALX148), cetuximab, and pembrolizumab.
 
• Re-evaluate on serial imaging.
 
• Consider patient referral to pulmonary specialist
 
• For recurrent pneumonitis, treat as Grade 3 or 4 event.
 
                                                                                                                                                                                                                                                                                                                                                                                                                                                                                                                                                                                                                                                                                                                   |
| Grade 2 (Symptomatic; medical intervention indicated; limiting instrumental ADL)             | 
 
• Evorpaccept (ALX148) may continue at the discretion of the investigator per medical judgment.
 
• Withhold pembrolizumab and cetuximab.
 
• Refer patient to pulmonary and infectious disease specialists and consider bronchoscopy or BAL.
 
• If bronchoscopy is consistent with immune-related etiology, initiate treatment with 1–2 mg/kg/day oral prednisone or equivalent.
 
• If event improves to Grade 1 or better within 2 weeks, resume cetuximab (dose determined by institutional guidelines). May consider resuming pembrolizumab at fixed dose at discretion of investigator and medical monitor.a,b,c
 
• Permanently discontinue study treatments and contact Medical Monitor if event does not resolve to Grade 1 or better within 2 weeks (unless otherwise agreed between the Investigator and AGICC).a,b,c
 
• For recurrent events, treat as a Grade 3 or 4 event.
 
 |
| Grade 3 (Severe symptoms; limiting self care ADL; oxygen indicated)                          | 
 
• Hold evorpaccept (ALX148)
 
• Permanently discontinue pembrolizumab and cetuximab.
 
                                                                                                                                                                                                                                                                                                                                                                                                                                                                                                                                                                                                                                                                                                                                                                                                                                                                |

|                                                                                                                              |                                                                                                                                                                                                                                                                                                                                                                                                                                                                                                                                                                                                                                                                                                                                                                                |
|------------------------------------------------------------------------------------------------------------------------------|--------------------------------------------------------------------------------------------------------------------------------------------------------------------------------------------------------------------------------------------------------------------------------------------------------------------------------------------------------------------------------------------------------------------------------------------------------------------------------------------------------------------------------------------------------------------------------------------------------------------------------------------------------------------------------------------------------------------------------------------------------------------------------|
| OR

Grade 4 (Life-threatening respiratory compromise; urgent intervention indicated (e.g., tracheotomy or intubation)) | 
 
• Refer patient to pulmonary and infectious disease specialists and consider bronchoscopy or BAL.
 
• If bronchoscopy is consistent with immune-related etiology, initiate treatment with 1–2 mg/kg/day oral prednisone or equivalent.
 
• If pulmonary event does not improve within 48 hr or worsens, consider adding an immunosuppressive agent (e.g., infliximab, cyclophosphamide, IV Ig, or mycophenolate mofetil ).
 
• If event resolves to Grade 1 or better, taper corticosteroids over <math>\geq 1</math> month.
 
• If event resolves to Grade 1 or better, evorpacept (ALX148) may be resumed at 1 dose level lower if deemed appropriate by the Investigator and medical monitor.
 
 |
|------------------------------------------------------------------------------------------------------------------------------|--------------------------------------------------------------------------------------------------------------------------------------------------------------------------------------------------------------------------------------------------------------------------------------------------------------------------------------------------------------------------------------------------------------------------------------------------------------------------------------------------------------------------------------------------------------------------------------------------------------------------------------------------------------------------------------------------------------------------------------------------------------------------------|

IV: intravenous; BAL: bronchoalveolar lavage.

- If corticosteroids have been initiated, they must be tapered over  $\geq 1$  month to  $\leq 10$  mg/day oral prednisone or equivalent before pembrolizumab can be resumed. Add prophylactic antibiotics for opportunistic infections.
- The acceptable length of the extended period of time for which pembrolizumab can be held to allow for corticosteroids to be reduced to  $\leq 10$  mg/day oral prednisone or equivalent must be agreed upon by the investigator and the Medical Monitor.
- Resumption of pembrolizumab may be considered in patients who are deriving benefit and have recovered from the immune-related event (baseline or Grade  $\leq 1$ ). Patients can be rechallenged with pembrolizumab only after approval has been documented by both the investigator (or an appropriate delegate) and the Medical Monitor.

